
### Dose selection

Based on AstraZeneca studies,^29 30^ the Wisteria trial uses 3-day dosing, giving AZD1775 weekly to coincide with cisplatin administration thereby potentiating the DNA damage effects. The maximum total dose of AZD1775 1800 mg in combination with 1 dose of 40 mg/m^2^ cisplatin for group A is substantially lower than AZD1775 monotherapy dose 2250 mg every 21 days (225 mg two times per day orally over 2.5 days per week for 2 weeks per 21 day cycle) used in Do *et al*; and although in combination with cisplatin, the highest dose level (dose level 2) is likely to be safe.

A similar dose escalation algorithm will be carried out in group B with a higher acceptable target DLT level of 30% allowing for multiple dosing of cisplatin with radiotherapy in combination with AZD1775.^31–33^ Trial doses and schedule are set out in table 1. AZD1775 is administered orally. The feasibility of the oral administration will be evaluated in postoperative patients.

### Trial treatments

#### Group A (preoperative)

Patients will receive specified dose of AZD1775 by mouth (PO) two times per day at 12 hours intervals (2 hours before or after food) for 3 days, commencing on days 1 and 8, with 40 mg/m^2^ intravenous cisplatin delivered over 1 hour on day 8. A missed dose of more than 6 hours should be skipped. If vomiting occurs, patient should not retake the dose but wait until next scheduled dose. Surgery is not to exceed 42 days from start of neoadjuvant chemotherapy.

#### Group B (postoperative)

Patients will receive specified dose of AZD1775 PO two times per day for 3 days, commencing on days 2, 9, 23 and 30, and 40 mg/m^2^ intravenous cisplatin delivered over 1 hour on days 2, 9, 16, 23 and 30 (days are timed from the start of radiotherapy delivery). Radiotherapy (65 Gy and 54 Gy in 30 fractions given for 5 days per week over 6 weeks: D1-5, D8-12, D15-19, D22-26, D29-33, D36-40, to high-risk and low-risk volumes, respectively, as per Wisteria Radiotherapy Guidelines, see online supplementary appendices 3–6) will commence within 3 months of surgery and given concurrently with chemotherapy.

For both groups A and B, cisplatin dose banding is not permitted. BSA to be calculated according to local practice; if weight changes>10% then cisplatin dose should be recalculated.

AZD1775 (morning dose) should be administered prior to cisplatin, and group B to receive cisplatin 1 hour before radiotherapy; standard supportive treatment, including premedication with antiemetics (excluding aprepitant and fosaprepitant), is allowed according to standard practice guidelines.

### Trial outcome measures

#### Primary outcome measures

The recommended doses of AZD1775 (determined by the modified TITE-CRM) for group A and B.

Group A: the highest safe dose in combination with cisplatin with a predefined target DLT probability of 25% for up to 42 days from start of treatment.Group B: the MTD in combination with cisplatin/radiotherapy with a target DLT of 30% for up to 12 weeks from the start of treatment.Safety profile of AZD1775 in both group A and B.

#### Secondary outcome measure

Disease-free survival time for both groups and recorded from commencement of treatment to the date of disease recurrence, patient death or end of trial follow-up period.

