### Incorporating AZD1775 into clinical management

A recent randomised phase III study of neoadjuvant chemotherapy in a Chinese population with locally advanced resectable oral cavity cancer showed that docetaxel, cisplatin and 5-fluorouracil (TPF) treatment generated a response rate of 80%, with an exploratory analysis showing that clinical responders had improved overall survival and local control.^23^ There was no improvement in overall survival for the study group as a whole compared with the control group without upfront TPF chemotherapy, possibly because patients who would ordinarily have received POCRT received PORT alone in this study. In an earlier study, TP53 mutation conferred increased resistance to preoperative cisplatin-based chemotherapy in oral cancer.^24^ While neoadjuvant chemotherapy has yet to find a definitive role prior to surgery, these findings raise the possibility that chemosensitisation may further improve outcomes.

The preoperative group A sets out to test this hypothesis by combining 1 week of AZD1775 alone, with a second week of cisplatin (40 mg/m^2^) with AZD1775. This short course of treatment will minimise any delay between diagnosis and definitive surgery and prevent unacceptable delay for the non-responders from getting standard treatment. If this is a promising combination, the long-term aim is to test AZD1775 in the neoadjuvant setting to downstage the disease through treatment with cisplatin and AZD1775 in the preoperative setting, which may decrease the extent of surgery, and may also reduce the need for PORT/POCRT by reducing the involved margin rate. Many patients with tumours that have high-risk histopathological features develop relapsed disease within the anatomical area treated to a high radiation dose. Chemosensitisation and radiosensitisation via inhibition of the G_2_/M checkpoint by AZD1775 has the potential to improve outcomes with acceptable toxicity. This possibility is the basis of the treatment delivered in the group B cohort.

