## Methods

### Wisteria trial objectives

Primary objectives are to determine the recommended dose and safety profile of AZD1775 with cisplatin in the group A preoperative (window-of-opportunity) setting, and with cisplatin/radiotherapy in the group B postoperative setting. Other objectives: obtain information regarding group A and B disease-free survivals; evaluate AZD1775 pharmacodynamic (PD) effects when administered with cisplatin (group A); identify and correlate potential predictive biomarkers with PD markers of DNA damage (group A); determine the rate of R0, R1 or R2 resection status and surgical complication (group A); and group B quality of life (QoL).

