### Patient population, screening and consent

Group A patients are those with biopsy-proven squamous cell carcinoma of the oral cavity, larynx or hypopharynx (having accessible tumours for rebiopsy under local anaesthetic or via ultrasound-guided biopsy), and due to undergo surgery. Patients in group B consist of those already diagnosed with oral cavity, larynx or hypopharynx squamous cell carcinoma, who have undergone surgery and are considered at risk of relapse after surgery (ie, with positive margins and/or nodal extracapsular spread). Patients with cancer of the oropharynx will not be included. Since Human papillomavirus (HPV) is only routinely tested in oropharyngeal squamous cell carcinoma or unknown primary of squamous cell carcinoma in the National Health Service (NHS), HPV status was not determined or requested for the tumours as part of the study. Patients who meet the criteria will be supplied with the patient information sheet. If informed consent (online supplementary appendices 1 and 2) is given, the patient undergoes a full screening evaluation to ensure they satisfy the eligibility criteria prior to registration (boxes 1 and 2).

10.1136/bmjopen-2019-033009.supp1Supplementary data

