### Discontinuation of investigational medicinal product

Patients should discontinue trial treatment in the following circumstances: intolerable toxicity; confirmed disease recurrence; pregnancy; severe non-compliance to protocol; development of any study-specific criteria for discontinuation and investigator decision, for example, if the patient requires a prohibited concomitant medication.

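### Group A disease-free survival starts with tumour in place but has no event for progression before surgery, unresectable disease or R2 resection

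*Protocol article*

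**What the plan says.** The section Secondary outcome measure of the protocol article defines DFS once, for both groups, with time "recorded from commencement of treatment to the date of disease recurrence, patient death or end of trial follow-up period".

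The groups stand at different points in their disease course when that clock starts. Under Patient population, screening and consent, group A patients are described as "having accessible tumours for rebiopsy under local anaesthetic or via ultrasound-guided biopsy), and due to undergo surgery", while group B patients have already had their operation. For group A, the treatment section adds: "Surgery is not to exceed 42 days from start of neoadjuvant chemotherapy".

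One of the Wisteria trial objectives is to "determine the rate of R0, R1 or R2 resection status and surgical complication (group A"). Under Analysis of outcome measures, positive margins in group A are reported as a number and percentage, with no link to DFS. The same section has DFS analysed separately by group with Kaplan-Meier after 12 months of follow-up, and gives the median with a 95% CI where appropriate. The only disease event among the reasons for stopping trial treatment is "confirmed disease recurrence"; progression is not named.

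**The concern.** Recurrence presupposes a time at which the patient was free of disease. Group B patients have been resected before time zero, so recurrence or death is a workable event list. No group A patient is free of disease at time zero, and some may never become so: their tumour may progress before the operation, become unresectable, or be left in part at an R2 resection. Such a patient has persistent or progressive disease, not recurrence. Under the stated list, the only event left for that patient is death.

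At stake is what the group A curve means. The patients with the poorest local outcome after the preoperative window would contribute long disease-free times, and a later reader could take the curve as evidence on disease control after the window.

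**Working it through.** **Step 1: what the definition covers in group A.** The rule was set against each possible course after time zero.

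| Course in group A | Event under the stated rule | Free of disease at any time |
|---|---|---|
| Complete resection, later relapse | Yes, at recurrence | Yes |
| Death from any cause | Yes, at death | Either |
| Progression before surgery, alive | None | No |
| Becomes unresectable, alive | None | No |
| R2 resection, alive | None | No |

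No other section fills the last three rows. The objectives and tertiary outcomes tabulate resection status, the analysis section adds only the estimator and the median, and the discontinuation section speaks only of recurrence.

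**Step 2: direction.** Making these courses events can only add events or bring them forward. The curve under the stated rule therefore lies on or above the curve that counts them. A patient who progresses and then dies within 12 months is an event by month 12 under either rule, but an earlier one if progression counts.

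**Step 3: size, as illustration only.** The article states no DFS rate, event count or power for DFS, so there is no figure to reproduce. The one input from the document is the maximum of 21 patients per group (Trial design). The following are assumed: full recruitment, complete 12-month follow-up, e patients with recurrence or death by 12 months, and k further patients who progressed, became unresectable or had R2 resection and are alive with no recurrence recorded. With no earlier censoring, Kaplan-Meier reduces to a proportion:

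- DFS as written = 1 − e/21
- DFS with these patients as events = 1 − (e + k)/21
- difference = k/21, so 1/21 = 4.8 percentage points per patient

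| e (assumed) | k (assumed) | As written | Counted as events |
|---|---|---|---|
| 6 | 1 | 15/21 = 71.4% | 14/21 = 66.7% |
| 6 | 2 | 15/21 = 71.4% | 13/21 = 61.9% |
| 8 | 2 | 13/21 = 61.9% | 11/21 = 52.4% |
| 8 | 3 | 13/21 = 61.9% | 10/21 = 47.6% |

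The planned summary is the median. Among these rows its status changes only in the last: it is not reached by 12 months as written, and it is reached when the three patients count.

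**Step 4: how likely at least one such patient is.** For an assumed share p, the chance among 21 is 1 − (1 − p)^21:

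- p = 5%: expected 1.05 patients, chance 1 − 0.95^21 = 66%
- p = 10%: expected 2.1 patients, chance 1 − 0.90^21 = 89%
- p = 20%: expected 4.2 patients, chance 1 − 0.80^21 = 99%

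The document supports none of these shares. They show only that a few affected patients would matter at this sample size.

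**The case against.** The strongest reply is that the article condenses a fuller protocol. How to code a patient who never becomes disease-free may be settled there or in the analysis plan, and an investigator might record progression as recurrence in any case. This stands in part: a rule elsewhere cannot be excluded, which is why the point is about the literal reading. But the article does not leave the definition open. It states an origin and an event list for both groups, and that list does not fit group A. A convention left to each site would be a reason to write the rule down.

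It is also fair that DFS is secondary, single-arm and descriptive, that doses are chosen on dose-limiting toxicities alone, and that poor group A outcomes are visible elsewhere, through toxicity-delayed surgery, margin status, surgical complications and deaths. All of this stands and limits the consequence. The article names the median, not a 12-month rate, so the percentages above are illustrative.

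A reader might infer three stronger points that the document does not support:

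- **That the end of follow-up is treated as an event.** It is listed as a date at which the recorded time stops, and the choice of Kaplan-Meier implies censoring there.
- **That surgery is delayed by six weeks.** The 42 days is a ceiling from start of treatment to surgery. No usual waiting time is given, so no added delay can be derived.
- **That R2 cases are expected.** R0, R1 and R2 are the complete classification, and listing a category does not forecast it. Eligibility requires a multidisciplinary recommendation for curative surgery and excludes metastatic disease. The stated aim of the short course, to "prevent unacceptable delay for the non-responders from getting standard treatment", concerns lack of response, not progression or inoperability.

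**Conclusion.** The point holds as a defect in a stated definition. One rule serves both groups, and in group A it gives no event to patients alive with disease that progressed before surgery, became unresectable or was left behind at R2 resection. Followed literally, it credits them with disease-free time and biases group A DFS upward.

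The size is unknown. At most it is 4.8 percentage points at 12 months per affected patient alive, given 21 patients, complete follow-up and no recurrence recorded for that patient. It is zero if no such patient occurs. The dose recommendation, the stopping rules and group B DFS are not touched. The definition should be corrected, but the trial's primary conclusions do not depend on it.

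**What to change.** For group A, keep start of treatment as the origin and report event-free survival. The events and their dates would be:

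- progression before surgery, or progression that precludes surgery: date of progression
- R2 resection: date of surgery
- recurrence after resection: date of recurrence
- death: date of death

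Report patients unresected for other reasons, such as declining surgery, separately, and add a sensitivity analysis that counts them as events. Counting every non-resection as failure in the main analysis is debatable, since such a patient may be controlled by other treatment. Starting the clock at R0 or R1 resection is not a good substitute, because it selects patients on an outcome that follows trial treatment. Group B can keep the present definition.

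The change is mainly one of wording. Resection status is already planned data, and the time to surgery is needed for the dose-limiting toxicity rule. The article does not show that the date of pre-surgical progression is recorded, nor the date of a decision not to operate, which the sensitivity analysis would need. Both should be checked on the data forms. The other cost is a less favourable group A figure if such patients occur.

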#### Tertiary research outcome measures

PD effects of AZD1775 and correlation with TP53 mutation status; pharmacokinetic (PK) effects of AZD1775 will be determined; optimise, validate and test feasibility of assays to investigate serum, ctDNA and RNA biomarkers; investigate the feasibility of immune function testing in a multicentre setting; complete pathological response rate for group A; positive resection margin status in group A; surgical complication in group A; and QoL in group B using European Organization for Research and Treatment of Cancer (EORTC) C30 (V.3.0),^34^ EORTC QLQ-H&N35^35^ and M.D. Anderson Dysphagia Inventory,^36^ as summarised in table 2.

**Table 2 T2:** Trial summaries of group A and group B

**Summary of** **g** **roup A**	
Setting	Patients undergoing surgical resection
Design	Modified TITE-CRM
Chemotherapy	Cisplatin 40 mg/m^2^ intravenous over 1 hour on day 8
AZD1775	AZD1775 PO BID for 3 days on days 1–3 and 8–10 dose-recommendation according to the modified TITE-CRM model
Surgery	Resection within 42 days of start of neoadjuvant treatment
DLT reporting period	The minimal reporting period is 30 days from start of treatment, but patients will be monitored up to 42 days for delay in surgery due to treatment-related toxicity
PK samples	Pharmacokinetic samples will be collected pre and post—the fifth dose of AZD1775 on days 3 and 10 (4 samples per patient)
PD markers	Assess CDK1, pCDK1, γH2AX, p53, p16, HH3, pHH3, Ki67, C3, CC3, p21, WEE1, pWEE1, PDL-1 and TILS, and other markers of particular interest
Follow-up	Clinically for at least 12 weeks from start of treatment
**Summary of** **g** **roup B**	
Setting	Postoperative patients with high-risk disease (involved resection margins +/or extracapsular nodal spread) receiving chemoradiation
Design	Modified TITE-CRM
Chemotherapy	Cisplatin 40 mg/m^2^ intravenous over 1 hour on day 2 of weeks 1–5 of radiotherapy
Radiotherapy	External beam radiation therapy (30 fractions over 6 weeks) to start within 3 months of surgery. Dose levels are 65 Gy for positive margin, 60 Gy to lymph node levels that have been dissected and 54 Gy to elective lymph node areas. A dose of 65 Gy may also be applied to areas of gross extracapsular spread at the discretion of the treating clinician.
AZD1775	AZD1775 PO BID for 3 days on days 2–4 of weeks 1, 2, 4 and 5 (no treatment with AZD1775 during weeks 3 and 6). Dose recommendation will be according to modified TITE-CRM model.
DLT reporting period	The minimal reporting period is 56 days (8 weeks) from start of radiotherapy, but patients will be monitored for DLTs up to 84 days (12 weeks), that is, up to 6 weeks from the end of POCRT
PK samples	Pharmacokinetic samples will be collected pre and post—the fifth dose of AZD1775 on week 1—day 4 (2 samples per patient)

DLT, dose-limiting toxicity; PD, pharmacodynamic; PK, pharmacokinetic; POCRT, postoperative chemoradiation; TITE-CRM, time-to-event continual reassessment method.

Assessment data will be collected as listed in online supplementary appendix tables 7 and 8.

### DLT and dose management

Predefined DLTs have been specified by the Clinical Investigators (box 3), and recorded toxicity profiles for the Wisteria treatments are given in online supplementary appendix table 9. Toxicity is assessed using the National Cancer Institute Common Terminology Criteria for Adverse Events V.4.0^37^ unless otherwise specified. Any patient requiring a toxicity-related dose delay of more than 21 days must be discontinued from the study unless there is approval from the chief investigator for the patient to continue. For group A, if any treatment-related grade≥3 toxicity develops in week 1, cisplatin and AZD1775 are discontinued in week 2. For group B, if calculated GFR falls below 60 mL/min, immediately before any cycle of concomitant chemotherapy, weekly cisplatin should be discontinued and consideration given to substitute with weekly carboplatin (Area Under the Curve (AUC)=1.5), according to routine local practice.

Box 3Dose-limiting toxicities (DLT)Patients experiencing any of the following adverse reactions (ARs) during the reporting period will be considered to have experienced a DLT:Grade 3 or 4 neutropenia lasting for >7 days despite adequate granulocyte-colony stimulating factor (G-CSF) support.Grade 4 febrile neutropenia, which includes grade 3 febrile neutropenia accompanied by systemic inflammatory response syndrome/sepsis or other life-threatening consequences.A third occurrence of grade 2 or worse neutropenia despite G-CSF support.Grade 3 or 4 thrombocytopenia lasting ≥7 days.Any occurrence of grade 4 anaemia.Any occurrence of grade 4 mucositis.Any occurrence of grade 3 nausea despite preventative and supportive care according to local practice. Tube feeding is not considered a DLT.Any occurrence of grade 4 vomiting despite preventative and supportive care according to local practice. Tube feeding is not considered a DLT.Any occurrence of grade 4 diarrhoea despite preventative and supportive care according to local practice.Any AR which results in an omission of chemotherapy administration and/or study treatment for >14 days.A start-of-treatment-to-surgery time of >42 days in group A as a result of a treatment-related toxicity.Grade 3 mucositis lasting >42 days after the end of treatment in group B.An overall treatment time of >49 days from the first day of radiotherapy in group B as a result of a treatment-related toxicity.Any grade 3 or 4 non-haematological AR (except for fatigue, nausea, vomiting and diarrhoea) for which medical intervention that lasts >7 days is required and the investigators deem that this AR is more severe or prolonged than what would be expected of standard treatment. Tube feeding is not considered a DLT.Any clinically significant occurrence which investigators within the trial management group agree would place the patient at undue safety riskIf the inability to swallow the AZD1775 capsule develops during the course of trial treatment, this event should be noted in the relevant section on the Suspected DLT form and reported immediately. However, this is not considered a DLT in itself.

In both groups, a full blood count is obtained at the beginning of each week. If haematological toxicity occurs, treatment should be modified as per online supplementary appendix tables 10 and 11. For non-haematological toxicities, treatment should also be modified as per online supplementary appendix tables 12–16.

The selection of PD markers to test are different for group A and group B as group A enables examination of samples pretreatment and post-treatment with AZD1775.

### Concomitant medications

All concomitant medications received within 14 days before the first dose of study medication and for 12 weeks after the last dose of study medication should be recorded. Medications may be administered for maintenance of existing conditions prior to study enrolment or for a new condition that develops while on study. The treatments and medications listed in online supplementary appendix 17 are prohibited or to be used with caution while in this study. No other investigational therapy or anticancer agents, other than the study medications, should be given to patients. If such agents are required for a patient, then the patient must first be withdrawn from the study. Live vaccines are not permitted.

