#### Practical considerations

Restriction is applied to avoid skipping of untried doses in escalation.Stop early due to safety concerns if there is sufficient evidence that the posterior probability of DLT at the lowest dose is greater than the target DLT rate, implying that the lowest dose is too toxic.Stop early if sufficient patients have been allocated to the current MTD (and remains the recommended dose level for the next cohort if the trial continues) before the full recruitment of 21 patients.The minimum DLT period is set at 30 days for group A and 8 weeks for group B. This means that partial information of no DLT in a patient can only be included in the model if they have been followed up for at least 30 days or 8 weeks in group A and B, respectively. (The full DLT assessment periods are 42 days and 12 weeks in group A and B, respectively.) This feature can easily be accommodated using the TITE-CRM model.A ‘look ahead’ strategy will be implemented if the next recommended dose level by the modified TITE-CRM model will not be influenced by the outcome of the remaining patient(s) of a particular cohort (DLT or no DLT). By implementing this strategy, the next cohort can be recruited immediately without awaiting the final observations from the current cohort, thus reducing waiting time between cohorts.

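### Group B's carboplatin option triggers a rule that withdraws the patient from the study; this conflicts with the sections on stopping treatment and safety follow-up and leaves late DLT observation in doubt

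*Protocol article*

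**What the plan says.** All references are to the protocol article.

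- *Concomitant medications*: "No other investigational therapy or anticancer agents, other than the study medications, should be given to patients". The next sentence reads: "If such agents are required for a patient, then the patient must first be withdrawn from the study". No exception is named.
- *DLT and dose management*: in group B, if calculated GFR is below 60 mL/min just before a cycle, "weekly cisplatin should be discontinued and consideration given to substitute with weekly carboplatin".
- The same section has a rule on long delays, with a waiver: "toxicity-related dose delay of more than 21 days must be discontinued from the study unless there is approval from the chief investigator".
- *Discontinuation of investigational medicinal product*: "Patients should discontinue trial treatment in the following circumstances: intolerable toxicity; confirmed disease recurrence". The list ends with investigator decision, and its example is a patient who needs a prohibited drug. The act described is stopping trial treatment, not leaving the study.
- *Analysis of outcome measures*: safety is followed in everyone who has had at least one dose, to the end of follow-up.
- Box 3 counts as a DLT: "Any AR which results in an omission of chemotherapy administration and/or study treatment for >14 days".
- *Statistical methodology*: a patient with a DLT has full weight. Partial information is provided for when withdrawal, discontinuation or death is unrelated to treatment.
- *Practical considerations*: "partial information of no DLT in a patient can only be included in the model if they have been followed up for at least 30". That figure is in days and applies to group A; the one for group B is 8 weeks.

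**The concern.** The listed trial treatments are cisplatin, AZD1775 and, in group B, radiotherapy (Table 1). Carboplatin is not among them. A site that takes up the carboplatin option and also obeys the *Concomitant medications* section must withdraw the patient from the study for a step that the protocol itself offers. The section on discontinuation would have the same site stop trial treatment only, and the analysis section would have it keep following the patient.

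The primary outcome is at stake. Group B's recommended dose rests on DLTs observed for up to 12 weeks. If withdrawal is taken to end follow-up, a patient who is DLT-free at the switch has too little follow-up to enter the model, and *Trial design* allows unevaluable patients to be replaced. Falling renal function during cisplatin may be treatment-related, and the article makes no provision for treatment-related withdrawals in the model.

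**Working it through.** **1. Timing of a carboplatin switch.** Inputs: cisplatin on days 2, 9, 16, 23 and 30, counted from the start of radiotherapy (*Group B (postoperative)*); minimum follow-up 56 days and full window 84 days, from the same start (Table 1). GFR is judged immediately before a cycle, so the cisplatin days date the switch. Share of window = day / 84; shortfall = 56 − day.

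| Switch at day | Share of 84 days | Days short of 56 |
|---|---|---|
| 2 | 2% | 54 |
| 9 | 11% | 47 |
| 16 | 19% | 40 |
| 23 | 27% | 33 |
| 30 | 36% | 26 |

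The minimum is 56/84 = 67% of the window, so no switch day comes near it. Even the latest leaves 84 − 30 = 54 days of the window unobserved. A switch on day 2 or 9 may already fail the requirement of two weeks of treatment as scheduled. The withdrawal rule therefore matters most clearly on days 16, 23 and 30, when a patient can meet that requirement and still miss the follow-up minimum.

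**2. Late DLTs.** Two group B criteria in Box 3 cannot be met by day 30. One is an overall treatment time above 49 days. The other is grade 3 mucositis lasting more than 42 days after the end of treatment. With radiotherapy ending on day 40 as scheduled, the second is met only after day 40 + 42 = 82, just inside the 84-day window.

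**3. The delay rule.** The DLT criterion is passed at dose day + 14 and the study-discontinuation rule at dose day + 21. A delay is taken here to be an omission for that time.

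- Group A, day 8 dose: day 22 against day 29, window 42.
- Group B, doses on days 2, 9, 16, 23, 30: days 16, 23, 30, 37, 44 against days 23, 30, 37, 44, 51, window 84.

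The DLT always comes 7 days earlier and inside the window, and it keeps full weight. No DLT information is lost under this rule.

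**4. Size and direction.** The article gives no switch rate and no DLT rate after a switch, so these counts are assumptions. Suppose full follow-up of 21 patients would show 7 DLTs (7/21 = 33.3%), and 4 patients leave before any DLT.

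- 2 of the 4 would have had a later DLT: 5/17 = 29.4%, lower.
- 1 of the 4: 6/17 = 35.3%, higher.
- None of the 4: 7/17 = 41.2%, higher.

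The direction depends on whether the lost patients' DLT rate is above or below that of the rest. These are crude pooled proportions; the TITE-CRM fits a curve over up to four dose levels.

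**The case against.** A reader might infer that both rules remove the patients with most toxicity from DLT, safety and DFS follow-up and so push the recommended dose upward. The article does not support that.

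- The delay rule costs no DLT data (step 3), and the chief investigator can waive it.
- Loss of safety and DFS follow-up is nowhere stated. *Analysis of outcome measures* monitors dosed patients to the end of follow-up, *Safety monitoring* sets its reporting windows without a cut-off at withdrawal, and DFS ends at recurrence, death or end of follow-up.
- The switch is optional and in group B only. Its trigger of 60 mL/min is also the entry threshold in Box 1, so a small fall can set it off.
- Some switched patients may already have a DLT for omitted chemotherapy. The article does not say whether replaced cisplatin counts as omitted.
- *Statistical methodology* provides for partial data after unrelated withdrawals but does not expressly exclude the rest.
- Follow-up after withdrawal is often left to the full protocol, and the appendix listing prohibited drugs is not shown.

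All of this stands and limits the point. It does not remove the conflict: the withdrawal sentence is unqualified, the carboplatin option falls within its words, and two other sections say something different. The finding rests on what the article states, not on what it leaves out.

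**Conclusion.** The point holds as a contradiction in the text that reaches the primary outcome in group B. Read literally, a switched patient leaves the study by day 30, at least 26 days short of the minimum for counting DLT-free follow-up and before the two late DLT criteria can be met. No handling is stated for a treatment-related withdrawal.

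This rests on two assumptions: that sites apply the withdrawal sentence to carboplatin, and that they take withdrawal to end DLT observation. If either fails, no DLT data are lost and only the wording is at fault. How many patients are affected, and which way the estimated DLT rate would move, cannot be derived from the article. For delays over 21 days, only later AE and DFS follow-up is at issue.

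**What to change.** 1. Reconcile *DLT and dose management*, *Concomitant medications*, *Discontinuation of investigational medicinal product* and *Analysis of outcome measures* on whether a long toxicity delay, or the need for another agent, ends trial treatment or study participation.
2. Say how the carboplatin option stands against the bar on other anticancer agents. Which clinical rule applies is for the sponsor to decide.
3. Whatever that decision, state that DLT, AE/SAE and DFS follow-up continues for the full windows unless the patient withdraws consent.
4. Keep switched patients in the DLT data with their observed follow-up and a flag for the switch, and say whether replaced cisplatin counts as omitted chemotherapy under Box 3.
5. State how treatment-related withdrawals enter the TITE-CRM, including their weight before 56 days.

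The cost is wording, one flag in the data, and some further follow-up records. The 21-patient maximum and the dose levels need not change.
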